### 2.7 Reference standards

Although the true 'gold standard' would be histology on all lesions, this would not be practical or ethically acceptable for every participant. In clinical practice, an expert opinion is considered the practical 'standard' of whether or not a pigmented lesion is 'clinically significant' in requiring monitoring or biopsy.

#### 2.7.1 Referred lesions

All lesions considered 'suspicious' by a Lead Clinician from both trial arms are referred to secondary care (Addenbrooke's Hospital) via the normal two-week skin cancer care pathway, where one of three dermatologists (Experts A, B and C) provide an opinion as to whether or not the pigmented lesion is 'clinically significant'.

#### 2.7.2 Non-referred lesions

All lesions considered 'not suspicious' by a Lead Clinician, and therefore not referred, are assessed three months later by two other skin cancer experts (Experts D and E). The expert assessment includes review of the seven-point checklist, the digital photograph and, for intervention group participants, the MoleMate images to make the final reference standard diagnosis of 'suspicious' or 'not suspicious'.

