#### Intervention group

Prior to commencing patient recruitment, Lead Clinicians complete a MoleMate Training CD-rom which teaches users to identify relevant SIAscopic features of various pigmented skin lesions. The Training CD-rom takes up to 2 hours to complete and has been shown to significantly improve GPs' ability to interpret SIAscopic images [22]. Participants in the intervention arm have their lesion/s assessed according to the same 'best practice' principles in the comparison arm. Lead Clinicians then use the MoleMate system to support their assessment and management of the lesion.

For all lesions an Index of Suspicion scale is completed, and the clinical diagnosis and intended action recorded (suspicious and refer via the two-week cancer route, or benign and reassure). A digital photograph is taken of every lesion for expert review.

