#### 2.9.2 Secondary outcomes

##### Related to the primary outcome

- Volume of referrals: there is a possibility that the proportion of appropriate referrals will be the same in the Intervention and Comparison groups despite differences between these groups in the number of total referrals (denominator) and the number of clinically significant lesions (numerator). The primary outcome measure will be unpacked to examine the total number of referrals (i.e. volume) and the number of clinically significant lesions in each group;

- Sensitivity, specificity and negative predictive value (NPV) of the decision not to refer using data from all lesions in the trial.

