#### Secondary outcomes

##### 1. Related to the primary outcome

*1.1 Volume effects*

The volume of referrals will be measured by the percentage of randomised participants over the study period who are referred by Lead Clinicians to secondary care, and compared between randomised groups as a difference in proportions with 95% confidence interval for the difference, and using the chi-squared test.

*1.2 Sensitivity, specificity and negative predictive value of the decision not to refer*

Sensitivity, specificity and other study proportions of lesions will be analysed using the same approach as for the primary outcome measure. These data will be used to compare the PPV of a referral (the primary outcome), and the NPV (correct management of lesions not referred) which will provide important data around lesions which are incorrectly identified as not suspicious in general practice. These data can contribute to further development of the diagnostic algorithm embedded in the MoleMate system.

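### Experts judging non-referred lesions see the MoleMate images in the intervention arm only, so the between-arm comparisons of sensitivity and NPV are liable to bias of unknown direction and size

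*Protocol article*

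**What the plan says.** Section 2.7.2 sets the reference standard for lesions that the Lead Clinician does not refer. Two skin cancer experts, D and E, assess them three months later and reach a binary verdict on suspicion. In both arms they have the checklist and the photograph before them. One arm gets a further item: "for intervention group participants, the MoleMate images to make the final reference standard diagnosis of". Comparison-arm lesions are thus judged on two pieces of evidence and intervention-arm lesions on three.

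The third piece comes from the system that informed the decision being judged. Section 2.6 (Intervention group) says: "Lead Clinicians then use the MoleMate system to support their assessment and management of the lesion".

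Referred lesions follow another route. Under 2.7.1, "one of three dermatologists (Experts A, B and C) provide an opinion as to whether or not the pigmented lesion is 'clinically significant"; no use of MoleMate images is stated there.

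Section 2.9.2 lists as secondary outcomes: "Sensitivity, specificity and negative predictive value (NPV) of the decision not to refer using data from all lesions in the trial". Section 2.11 (item 1.2) adds: "Sensitivity, specificity and other study proportions of lesions will be analysed using the same approach as for the primary outcome measure". For the primary outcome, that approach is a comparison of proportions between the randomised groups with allowance for clustering within patient.

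**The concern.** False and true negatives in this trial are whatever Experts D and E say they are. If the evidence put before them differs by arm, a difference in false negatives may come from the experts' material and not from the clinicians' decisions.

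There are two mechanisms. The first is incorporation: in the intervention arm the index technology is part of its own reference standard. An expert who sees the scan that reassured the clinician may be more inclined to agree, which would hide missed lesions. Equally, the scan may show an expert features that a photograph does not, which would add apparent misses in that arm only. The second is unmasking: the presence or absence of the images shows which arm the lesion came from.

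The stake is the reading of the primary result. PPV of referral can rise because clinicians become more accurate, or because they refer fewer lesions, including some that matter. Sensitivity and NPV help to tell these apart. Section 2.11 also says that these data may serve further development of the MoleMate algorithm; labels made partly from MoleMate images would make that use circular.

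**Working it through.** The protocol states no expected value, sample size or power for sensitivity, specificity or NPV, so there is no figure to reproduce. The check is how far the experts' calls alone can move these measures when clinicians perform identically in both arms.

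**Inputs from section 2.10:** target 1450 study lesions, 400 of them referred; 55% of referred lesions clinically significant in the combined interim data.

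**Assumptions:** equal arms; the same 55% in each arm; a rate f at which D and E call a non-referred comparison-arm lesion suspicious, taken as 2%, 5% or 10%; and a factor k by which the images multiply that rate in the intervention arm, taken as 0.5 or 2. The protocol gives neither f nor k.

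**Per arm:**
- lesions 1450/2 = 725; referred 400/2 = 200; non-referred 725 - 200 = 525
- TP = 200 × 0.55 = 110; FP = 200 - 110 = 90
- FN = 525 × f (comparison) or 525 × f × k (intervention); TN = 525 - FN
- sensitivity = TP/(TP + FN); NPV = TN/525; specificity = TN/(TN + FP)

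**Worked case, f = 5%:**
- Comparison: FN = 26.25; sensitivity 110/136.25 = 80.7%; NPV 498.75/525 = 95.0%; specificity 498.75/588.75 = 84.7%
- Intervention, k = 0.5: FN = 13.125; sensitivity 110/123.125 = 89.3%; NPV 97.5%; specificity 511.875/601.875 = 85.0%
- Intervention, k = 2: FN = 52.5; sensitivity 110/162.5 = 67.7%; NPV 90.0%; specificity 472.5/562.5 = 84.0%

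**Spurious difference, intervention minus comparison, in percentage points** (from unrounded values):

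| f | k | Sensitivity | NPV | Specificity | Chance of p < 0.05 for NPV |
|---|---|---|---|---|---|
| 2% | 0.5 | +4.2 | +1.0 | +0.1 | 27% |
| 2% | 2 | -7.3 | -2.0 | -0.3 | 48% |
| 5% | 0.5 | +8.6 | +2.5 | +0.3 | 57% |
| 5% | 2 | -13.0 | -5.0 | -0.7 | 87% |
| 10% | 0.5 | +13.0 | +5.0 | +0.7 | 87% |
| 10% | 2 | -16.5 | -10.0 | -1.6 | over 99% |

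The last column is Φ[(d - 1.96·se0)/se1], with d the NPV difference and se0 and se1 its pooled and unpooled standard errors at 525 per arm. For f = 5%, k = 0.5: d = 0.025, se0 = √(2 × 0.0375 × 0.9625/525) = 0.01173, se1 = √((0.05 × 0.95 + 0.025 × 0.975)/525) = 0.01170, giving Φ(0.17) = 57%, against a nominal 5%. Clustering of lesions within patients is ignored, so these chances are approximate.

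If both arms are read on the same material with arm masked, k = 1 and the artefact is zero by construction.

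**The case against.** The strongest reply is that the affected outcomes are secondary and are not the trial's only view of missed lesions. That stands. A reader might infer that nothing else shows whether MoleMate misses lesions, but the protocol does not support this. Five-year registry incidence and mortality are planned for all participants (2.9.2, 2.11), and the Discussion presents them as information on false negatives. Section 2.9.2 also counts clinically significant referrals in each arm; under randomisation a shortfall in one arm would point to missed lesions without any verdict from D or E. These checks are partial. The registry records melanomas only, and the Discussion concedes that melanoma detection as primary outcome would need a much larger trial. The six-month audit in 2.8 is less independent, because the experts compare its findings with the original trial data.

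A reader might also infer that the comparison is shown to be biased in MoleMate's favour. It is not: nothing in the protocol says how the images move the experts, and either direction is plausible.

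On masking, the article is silent, and a condensed article may leave reading order to the full protocol. But 2.7.2 states that the images go into making the final reference diagnosis, so the difference in evidence is stated design. Section 2.7 defends expert opinion in place of histology; it does not defend different evidence by arm.

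Finally, judging referred lesions as clinically significant in clinic and non-referred ones as suspicious on stored material is a separate matter. It applies to both arms and does not support the present point.

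**Conclusion.** The point holds. As described, the reference standard for non-referred lesions differs by arm and includes the index technology in one arm, so between-arm differences in sensitivity and NPV cannot be attributed to clinicians' decisions alone. Specificity is touched in principle but moves by at most 1.6 points in every scenario examined.

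The size is unknown. With f from 2% to 10% and k of 0.5 or 2, the artefact runs from +13.0 to -16.5 points in sensitivity and from +5.0 to -10.0 points in NPV. These figures show what the design permits; they do not estimate a bias.

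It would be wrong to extend the point to the primary analysis: PPV of referral uses referred lesions judged by Experts A to C and does not involve the D and E verdict. Because the outcomes concerned are secondary and partial independent checks exist, this is a should-fix.

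**What to change.** 1. Experts D and E record the reference verdict from the seven-point checklist and photograph alone, in both arms, masked to arm. Only this verdict enters sensitivity, specificity and NPV.
2. The MoleMate images are opened afterwards and any change of opinion is recorded separately. It serves the safety review in 2.8 and a sensitivity analysis, so no safety information is lost.
3. For lesions already assessed, stored photographs and checklists are re-read in random order with arm masked. At the September 2009 interim analysis this meant up to about 913 - 254 = 659 non-referred lesions. Results are reported separately for prospectively masked and re-read lesions.

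The material exists: the checklist is used in both arms, and "A digital photograph is taken of every lesion for expert review". No new patient procedures are needed. The cost is a revised read form and extra reading time, which is not trivial for a re-read of several hundred lesions. Two limits remain. Recall may weaken masking if the same experts re-read cases. The checklist is also part of the clinician's own assessment, so the change makes incorporation equal between arms without removing it.

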### 2.8 Safety procedures

All non-referred participants with a lesion considered 'suspicious' by Experts D and E are invited to an early review by the Lead Clinician to re-assess the lesion and thus ensure safety in the study. All other participants with 'not suspicious' lesions, as determined by Experts D and E, are invited to attend an Audit Appointment with the Lead Clinician six months after their first consultation. At this consultation the lesion is re-examined and the seven-point checklist and digital photograph repeated. Experts D and E compare these new data with the original trial data to ensure no potentially suspicious lesions are 'missed' within the trial. This safety-net procedure was introduced in response to concerns raised by the Research Ethics Committee.

### 2.9 Measurement

Table 1 summarises the content and timing of all the clinical and psychological measures.

**Table 1 T1:** Trial measures and timing.

		Time after 1^st ^Lead Clinician (LC) consultation				
	
		All participants			Non-referred participants	Referred participants
	
		1^st ^LC consultation	up to 1 week	3 months	6 months	within 2 weeks
**Clinical assessment of lesion(s)**		√			√	√
					
**Psychological measures (questionnaire)**						
Anxiety: short form STAI^†^			√	√		
Cancer worry: modified cancer worry scale			√	√		
Satisfaction with LC consultation^¥^			√			

^† ^Spielberger State-Trait Anxiety Inventory

^¥ ^Items from Europep instrument relating to the dimensions of care

#### 2.9.1 Primary outcome

The primary outcome is the positive predictive value (PPV) of the primary care decision to refer. This is defined as the proportion of referred lesions that are considered 'clinically significant' (biopsy or monitor) by secondary care experts, and is therefore the proportion of all referred lesions that are deemed 'clinically significant'. This is a measure of the appropriateness of a referral and, by implication, the diagnostic accuracy of the GP with or without the aid of the MoleMate system.

#### 2.9.2 Secondary outcomes

##### Related to the primary outcome

- Volume of referrals: there is a possibility that the proportion of appropriate referrals will be the same in the Intervention and Comparison groups despite differences between these groups in the number of total referrals (denominator) and the number of clinically significant lesions (numerator). The primary outcome measure will be unpacked to examine the total number of referrals (i.e. volume) and the number of clinically significant lesions in each group;

- Sensitivity, specificity and negative predictive value (NPV) of the decision not to refer using data from all lesions in the trial.

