## Methods/designs

### 2.1 Definitions

For the purpose of this trial, the definition of 'suspicious pigmented lesion' is any lesion presented by a patient, or opportunistically seen by a clinician in general practice, which cannot immediately be diagnosed as benign and the patient reassured.

The definition of 'appropriateness of referral' is whether the referred lesion is deemed 'clinically significant' by a dermatologist in a skin cancer clinic and is therefore either biopsied or monitored. Those lesions seen by a dermatologist in a skin cancer clinic which result in reassurance and discharge from the clinic without biopsy or monitoring are deemed 'clinically insignificant'.

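### Pooled sensitivity and specificity mix two reference standards chosen by the referral decision, so the between-arm difference in sensitivity can be distorted by an unknown amount

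*Protocol article*

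**What the plan says.** Section 2.9.2 lists "Sensitivity, specificity and negative predictive value (NPV) of the decision not to refer using data from all lesions in the trial". Section 2.11, item 1.2, has sensitivity and specificity analysed as the primary outcome is, that is, compared between randomised groups with allowance for several lesions per patient. It has no step for the way lesions were verified.

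- **Referred lesions** (2.7.1) go to the skin cancer clinic, "where one of three dermatologists (Experts A, B and C) provide an opinion as to whether or not the pigmented lesion is 'clinically significant". Section 2.1 gives the meaning: "deemed 'clinically significant' by a dermatologist in a skin cancer clinic and is therefore either biopsied or monitored".
- **Non-referred lesions** (2.7.2): "All lesions considered 'not suspicious' by a Lead Clinician, and therefore not referred, are assessed three months later by two other skin cancer experts". Their assessment "includes review of the seven-point checklist, the digital photograph and, for intervention group participants, the MoleMate images to make the final reference standard diagnosis", and the label is suspicious or not suspicious.

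Two other statements bear on the point. Section 2.9.2 says the primary outcome will also be broken down into the number of referrals and the number of clinically significant lesions in each group. Section 2.11, item 1.1, gives a randomised-participant denominator, a confidence interval and a test, but only for the percentage of participants referred.

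**The concern.** Sensitivity is true positives divided by true positives plus false negatives. Here the true positives are decided in clinic by Experts A to C, and the false negatives by Experts D and E from records. The experts, setting, information, timing and label all differ, and the Lead Clinician's decision to refer determines which set applies. This is differential verification.

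In a randomised comparison one might hope that the problem cancels. It need not, because MoleMate is intended to change which lesions are referred and so which standard each lesion receives. A lesion that the clinic would have monitored, if it is not referred and is then read as not suspicious, leaves the true positives and is counted as a true negative.

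PPV can rise simply because fewer lesions are referred. Sensitivity is one of the measures that a reader will use to judge whether a higher PPV came at the price of missed lesions.

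**Working it through.** **The plan's own figures.** The documents give no figure for sensitivity or specificity. The nearest are in section 2.10, and they reproduce: 254/913 = 27.8% referred (stated 28%); 0.28 × 1450 = 406 referred lesions (target 400); odds ratio for 45% v 60% = (0.60/0.40)/(0.45/0.55) = 1.83 (stated 1.8).

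**Inputs.** From section 2.10: 1450 lesions, 28% referred, PPV 45% and 60%. Assumed: 725 lesions per arm; the 28%, which is a combined-arm figure, applied to the comparison arm; true sensitivity on the clinic standard 90% (comparison) and 75% (MoleMate). Let *d* be the share of truly significant non-referred lesions that Experts D and E call suspicious. The documents do not give *d*.

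**Counts.**
- Comparison arm: referred 0.28 × 725 = 203; true positives 0.45 × 203 = 91.4; all significant lesions 91.4/0.90 = 101.5; missed 10.1.
- MoleMate arm: true positives 0.75 × 101.5 = 76.1; referred 76.1/0.60 = 127; missed 25.4.

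**Sensitivity as planned** = TP / (TP + *d* × missed).

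| *d* comparison / MoleMate | Comparison | MoleMate | Difference (points) |
|---|---|---|---|
| 1 / 1 | 90.0% | 75.0% | 15.0 |
| 0.8 / 0.8 | 91.8% | 78.9% | 12.9 |
| 0.5 / 0.5 | 94.7% | 85.7% | 9.0 |
| 0.2 / 0.2 | 97.8% | 93.8% | 4.1 |
| 0.5 / 0.2 | 94.7% | 93.8% | 1.0 |

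These percentages depend only on the assumed true sensitivities and on *d*, not on the counts. The last row is included because D and E see MoleMate images in one arm only, so *d* may differ by arm, in either direction.

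**Over-calling.** If D and E also call 5% of the other non-referred lesions suspicious, then with *d* = 0.5:
- Comparison: 5% of (725 − 203 − 10.1) = 25.6, so 91.4/(91.4 + 5.1 + 25.6) = 74.9%.
- MoleMate: 5% of (725 − 127 − 25.4) = 28.6, so 76.1/(76.1 + 12.7 + 28.6) = 64.8%.

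Sensitivity is lower in both arms, and the difference is 10.1 points.

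**Specificity.** Without over-calling, as *d* runs from 0.2 to 1 it stays within 82.1–82.3% (comparison) and 91.9–92.1% (MoleMate). Missed lesions are few beside the true negatives.

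**NPV and PPV.** NPV uses only non-referred lesions, all read by D and E. PPV uses only referred lesions, all judged in clinic. Neither mixes the standards, although NPV still depends on how well D and E read.

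**What separate rates would show.** Randomisation makes the expected number of truly significant lesions equal in the two arms. If the clinic standard is applied alike in both, the ratio of clinically significant referred lesions, 76.1/91.4 = 0.83, equals the ratio of true sensitivities, 75/90 = 0.83, whatever *d* is.

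**The case against.** A good deal can be said for the plan.

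- **The loss would be seen elsewhere.** The planned breakdown in section 2.9.2 would show about 91 v 76 clinically significant lesions in the scenario above, and the referral volume outcome would show the drop in referrals. This largely stands. However, the count has no stated denominator, interval or test, while pooled sensitivity goes forward as an arm comparison.
- **Histology on every lesion is not feasible** (2.7). True, but nothing here asks for it.
- **The two labels may mean the same thing.** Section 2.7 describes expert opinion in terms of monitoring or biopsy, and 2.7.2 does not exclude lesions needing monitoring from the suspicious label. So a difference in threshold is not established. The differences in experts, setting and information are.
- **Other safeguards exist.** The five-year registry data put all participants on one standard, but for melanoma only. The six-month audit is a safety procedure by the same experts.

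A reader might infer more: that the plan would largely hide a loss of sensitivity. The documents do not support this. On the figures above it needs *d* of about 0.3 or less in both arms (at 0.3 the 15-point loss appears as 96.8% − 90.9% = 5.9), or a clearly lower *d* with MoleMate. At 0.8 only about 14% of the loss is masked. No value of *d* is given, and the planned counts would show part of the loss in any case.

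A reader might also propose that D and E read the photographs of referred lesions, since "A digital photograph is taken of every lesion for expert review", and so put all lesions on one standard. That does not solve the problem. Lesions that only the clinic would call significant are negative on the photograph standard in both arms, so failing to refer them would show as no loss of sensitivity at all.

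**Conclusion.** The structural point holds on the text: pooled sensitivity and specificity combine two reference standards, the decision under test selects between them, and the stated analysis does nothing about it. The between-arm difference in sensitivity can therefore be distorted, and randomisation does not prevent this.

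The size is conditional. The masking of the assumed 15-point loss runs from about 2 points to about 11 when D and E perform alike in both arms and do not over-call, and can go further in either direction if they do not. All of this rests on assumed true sensitivities and on a detection share that the documents do not give. The point is confined to secondary outcomes and in practice to sensitivity; the primary comparison is untouched. It is worth correcting because the remedy is cheap.

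**What to change.** In section 2.11, item 1.2, make the between-arm comparison of missed lesions two separate rates. Each stays on its own standard, has all randomised participants in the arm as denominator, and is reported as a difference with a 95% confidence interval:

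- (a) participants with at least one referred lesion found clinically significant in clinic;
- (b) participants with at least one non-referred lesion called suspicious by Experts D and E.

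Read the two together: a fall in (a) that is not matched by a rise in (b) is the pattern that pooled sensitivity would understate.

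Report pooled sensitivity and specificity as descriptive only, with a sensitivity analysis in which missed lesions are estimated as (S − fN)/(d − f). Here S is the number called suspicious among N non-referred lesions, and d and f are the detection and over-call shares, each varied over a stated range separately by arm. Leave the primary PPV and the NPV as they are, and do not add a photograph re-reading of referred lesions as the single standard.

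The cost is analysis wording and a little extra analysis, with no new data. Pooled sensitivity loses its status as a formal arm comparison. The replacement will not be precise: taking lesions as units and ignoring clustering, 91.4/725 = 12.6% v 76.1/725 = 10.5% is a difference of 2.1 points, with standard error √(0.126 × 0.874/725 + 0.105 × 0.895/725) = 1.7 points and a 95% interval of about −1.2 to 5.4. That uncertainty should be reported.
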